### Randomization

Investigators from the participating institutions will have 24-h access to a Web-based central randomization system that provides immediate and concealed allocation. Eligible patients will be centrally randomized (1:1) into either the H-ESD or C-ESD group using the Web-based computer program, the Universal Hospital Medical Information Network (UMIN) Internet Data and Information System for Clinical and Epidemiological research (INDICE)-Cloud version. Randomization will be performed using dynamic balancing, which uses the minimization method by tumor location (upper third or middle third of the stomach vs. lower third of the stomach), tumor size (0–9 mm vs. ≥10 mm), and operators’ experience with ESD (0–29 cases vs. ≥30 cases). Patients and investigators will not be blinded to the allocated treatment group, and a unique patient identification number will be entered into the system to ensure anonymity.

### Blinding

Not applicable.

### Study organization

The coordinating center will be established by the principal and coordinating investigators. The former will be responsible for overseeing the trial and the latter for supporting the local investigators in trial management and data recording at each participating institution. Core members of the team will meet at least once a month or more often as required during the trial period.

The steering committee will be established by the principal investigator, coordinating investigators, statisticians, and gastroenterology experts. They will monitor and evaluate the overall conduct of the trial and make recommendations regarding trial-related decisions.

An independent data and safety monitoring board will be established by experts independent from this study and its competing interests. They will monitor the trial’s progress and confirm that it has been conducted, recorded, and reported in accordance with the trial’s protocol and relevant laws, regulations, and guidelines. Both online and on-site monitoring will be used to review the trial processes. Investigators will review data on endoscopy reports, pathological results, and adverse events up to the first discharge and enter it into the INDICE cloud. They will review and manage the input data for each case.

Participants will be free to withdraw from participation at any time upon request. An investigator may terminate participation in the study if a participant meets a newly developed or not previously recognized exclusion criterion that precludes further participation, such as the occurrence of a clinical adverse event or other medical condition or situation where continuing participation would not be in the participant’s best interest. The IRB of Kyushu University may terminate the trial in the event of a safety problem.

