The H-ESD procedure will be performed, as described in detail elsewhere, using a SOUTEN high-frequency surgical knife [12, 19]. SOUTEN will be fixed with the snare closed, and only the distal tip will be exposed. Marking, injection, and mucosal incision will be performed in the same manner as described for C-ESD using the tip of the SOUTEN and an injection needle. After completing the circumferential incision, a partial submucosal dissection will be performed using the tip of the SOUTEN. Snaring of the lesion will be performed once the operator considers it possible to perform the resection in an en bloc manner. The open snare will be placed around the lesion, which will subsequently be resected by closing the snare and coagulation. H-ESD can also be switched to C-ESD if the operator considers snaring too difficult to perform. In such cases, the submucosal dissection will be performed until the specimen is retrieved.

Injection of the viscous material can be performed in both C-ESD and H-ESD using an injection needle, but it can also be done in C-ESD using an endo-knife. Hemostasis will be performed in both C-ESD and H-ESD using the tip of the devices if bleeding occurs or if the blood vessels are detected. If bleeding cannot be controlled using only an endo-knife, hemostatic forceps will be used.

Patients will be managed as after regular ESD, including being managed with intravenous nutrition and fasting. Patients will start to receive proton pump inhibitors, including potassium competitive acid blockers after ESD. Enteral diets will start within 2 or 3 days after ESD. If there are no serious adverse events (AEs), patients will be discharged approximately 1 week after ESD. If any AEs occur, investigators will immediately provide appropriate treatment and record it. The endoscopic treatment performed in this study is covered by the current medical insurance, and all costs associated with the study, including the treatment of AEs, will be charged and paid in accordance with the medical insurance system. There is no special compensation system for side effects caused by these treatments.

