#### Secondary outcomes

The secondary outcomes are as follows: time of the mucosal incision; time and speed of the submucosal dissection, with or without snaring; en bloc and complete resection, curability, determined by histological assessment of the resected specimen; endoscopic procedural adverse events, including intraoperative perforation, delayed perforation, and delayed bleeding; degree of the dissected submucosal layer before snaring; volume of the injection solution used; number and duration of hemostasis events using a hemostatic device during the procedure; thickness of the submucosal layer in the resected specimen; and whether there was handover to another operator.

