### Definitions

The FAS is defined as the enrolled patients excluding those who do not receive study treatment, those with serious non-compliance with ethical guidelines, and those with missing primary endpoint data. The per-protocol set is defined as patients included in the FAS, excluding those who do not meet the inclusion criteria and those with significant deviations from the study protocol. The ESD procedure time is defined as that from the beginning of the mucosal incision to the completion of tumor resection as described above. The ESD procedure time is divided into individual procedure times, namely the procedure time for the mucosal incision and submucosal dissection with or without snaring. The incision speed is defined as the circumferential length of the resected specimen/incision time (mm/min). With or without snaring, the dissection time is defined as the time from the beginning of the submucosal dissection to the completion of the tumor resection. The dissection speed, with or without snaring, is defined as the area of the resected specimen/the time of dissection, with or without snaring (mm^2^/min). The resected specimen will be flattened on the plastic plate, and the length (mm) of its long and short axes will be measured using a ruler. These measurements will be used to calculate the circumferential length (mm) and resected area (mm^2^). En bloc resection is defined as single-piece resection. Complete resection is defined as en bloc resection with free vertical and horizontal margins. Curability is divided into A, B, C-1, or C-2 based on the Japanese gastric cancer treatment guidelines [5]. Delayed bleeding is defined as clinical evidence of bleeding after the ESD procedure requiring endoscopic hemostasis or a blood transfusion. Perforation is diagnosed when mesenteric fat or intra-abdominal space is observed with a stomach wall defect during the ESD procedure or when free air is detected on X-ray or computed tomography scans after the ESD procedure is complete. When snaring is conducted for resecting the lesion, the degree of the dissected submucosal layer by the tip of the endo-knife will be assessed. The volume of the viscous solution injected using the injection needle will also be recorded. The number of hemostasis events using hemostatic forceps that occur before resection of the lesion will be counted. The time of hemostasis is defined as the cumulative time from the appearance of the hemostatic forceps on the monitor to the completion of hemostasis. Hemostasis using the endo-knife or prophylactic hemostasis for the vessels after ESD will not be recorded. The thickness of the submucosal layer in the resected specimen will be assessed just below the center of the lesion.

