### Serious adverse events

The following AEs will be considered to be serious AEs (SAEs): AEs that lead to death or life-threatening AEs, AEs requiring re-hospitalization for treatment or extension of the hospitalization period, AEs leading to persistent or marked disability or dysfunction, AEs that have the potential to cause birth defects in offspring, and AEs requiring treatment to prevent the above results, even if they do not result in immediate life-threatening events, death, or hospitalization.

The reporting procedure is as follows: If investigators are aware of the occurrence of SAEs, required reporting measures will be taken by the investigators, such as providing explanations to the enrolled patients and reporting to the principal investigator in accordance with the “standard procedure manual for handling serious adverse events in medical research for humans (Kyushu University)” and in compliance with the “Ethical Guidelines for Medical and Health Research Involving Human Subjects (Japan).” If a principal investigator is aware of the occurrence of SAEs, the principal investigator will also prepare an SAE report and submit it to the hospital director. The hospital director will then submit the report to the clinical trial ethics review committee. In addition, information regarding the occurrence of SAEs will be promptly shared with all investigators. The entire study will be discontinued if the clinical trial ethics review board deems it necessary.

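### Adverse-event entry ends at first discharge, about one week after ESD, while delayed bleeding and delayed perforation are secondary outcomes with no end time

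*Protocol article*

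**What the plan says.** All references are to the protocol article.

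- **Data window (Study organization).** Investigators review endoscopy reports, "pathological results, and adverse events up to the first discharge and enter it into the INDICE cloud". Data registration, handling, and retention makes that cloud the trial database that goes to final analysis.
- **Timing of discharge (Endoscopic procedures).** "If there are no serious adverse events (AEs), patients will be discharged approximately 1 week after ESD". The timing is approximate and conditional on there being no serious event.
- **Outcomes (Secondary outcomes).** The list includes "endoscopic procedural adverse events, including intraoperative perforation, delayed perforation, and delayed bleeding".
- **Outcome definitions (Definitions).** "Delayed bleeding is defined as clinical evidence of bleeding after the ESD procedure requiring endoscopic hemostasis or a blood transfusion". Perforation is also diagnosed "when free air is detected on X-ray or computed tomography scans after the ESD procedure is complete". Neither definition has a closing time.
- **Seriousness criteria (Serious adverse events).** The list includes "AEs requiring re-hospitalization for treatment or extension of the hospitalization period". Investigators who become aware of a serious event report it to the principal investigator. It then goes to the hospital director and the ethics committee, and is shared with all investigators. No cut-off at discharge is given for this route.

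**The concern.** The article does not merely leave the follow-up period unstated. It states a period for data entry, and that period is shorter than its own outcome definitions imply. A bleed after discharge that needs endoscopic hemostasis meets the definition of delayed bleeding but falls outside the entry rule.

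The loss would also be silent. The Hypotheses and data analysis section plans complete-case analysis because little missing data is expected. A patient who bleeds after discharge is not missing in that sense: the record is complete and shows no event. No missing-data rule would detect this.

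At stake is the safety side of the comparison. H-ESD is to be judged superior on procedure time alone, so delayed bleeding and perforation are among the few outcomes that could weigh against a time saving. The article's Abstract promises data on both benefits and risks.

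**Working it through.** **1. Sample size, to show that it is not touched.** Inputs from Sample size estimation: difference 0.2, SD 0.3 (log scale), power 80%, significance level 0.05 (two-sided in Hypotheses and data analysis), 1:1 allocation. A two-sample t-test needs 36.3 per arm, rounded up to 37, so 74 in total, with power 0.808. With 10% dropout, 74 / 0.90 = 82.2, and 74 × 1.10 = 81.4, which rounds up to 82. The plan's 74 and 82 are reproduced, and neither depends on adverse-event collection.

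**2. The sections side by side.**

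| Item | Start | End | Section |
|---|---|---|---|
| Delayed bleeding | after ESD | none stated | Definitions |
| Perforation found after the procedure | after ESD | none stated | Definitions |
| Re-hospitalization as a seriousness criterion | after first discharge, by its nature | none stated | Serious adverse events |
| Adverse-event entry in the database | not stated | first discharge | Study organization |

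The entry window closes before the outcome definitions do. An adverse event that leads to readmission can arise only after first discharge, so the entry rule as written does not cover it.

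**3. The window varies.** The one-week discharge applies to patients without serious events. A patient with a complication may stay longer and so be observed longer. The period at risk therefore depends on the patient's course and, across nine institutions, on local practice.

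**4. Possible size.** The documents give neither a delayed-bleeding rate nor the share of events after discharge, so both are assumed here. With n patients, risk p and late share s, the expected number of events is n × p and the expected number lost is n × p × s.

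Per arm, n = 82 / 2 = 41:
- Low end: 41 × 0.04 = 1.64 events; lost 1.64 × 0.20 = 0.33.
- High end: 41 × 0.06 = 2.46 events; lost 2.46 × 0.50 = 1.23.

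So 1.6–2.5 events are expected per arm, of which 0.3–1.2 are lost.

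Both arms together, n = 82, over wider assumptions. The chance of losing at least one event is 1 − (1 − p × s)^82.

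| p | s | Events expected | Events lost | Chance of losing at least one |
|---|---|---|---|---|
| 3% | 10% | 2.46 | 0.25 | 22% |
| 5% | 25% | 4.10 | 1.03 | 64% |
| 8% | 50% | 6.56 | 3.28 | 96% |

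**5. What a loss does to the comparison.** The recorded risk is p × (1 − s). If s is the same in both arms, the risk difference shrinks by the factor 1 − s, that is by 20–50% under the per-arm assumptions, and the risk ratio is unchanged in expectation. One patient in 41 is 1 / 41 = 2.4 percentage points, so a single lost event visibly moves an arm's rate.

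**The case against.** **Serious-event reporting is a second route.** It has no stated cut-off at discharge, and a readmission for bleeding would qualify. This stands in part. A reader might infer that late events cannot become known at all, or that every readmission is lost to the trial; the documents do not support that. But the route works only if an investigator is aware of the event, and nothing says that its reports are entered as outcome data. It limits the gap without closing it.

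**Re-hospitalization sits in a generic seriousness list and is not a trial outcome.** This is correct, and a seriousness definition wider than the entry window is not by itself a contradiction. The point rests mainly on delayed bleeding and delayed perforation, which are named outcomes.

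**Unequal under-counting between arms is speculative.** This stands. A reader might infer from the open-label design and the variable discharge date that one arm would be under-counted more. The article describes one post-procedure course for both arms, and nothing indicates that discharge timing differs. A difference is possible but not shown.

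**This is a condensed article, and the SPIRIT diagram is not visible.** A later assessment may appear in the diagram or the full protocol, which limits confidence that no follow-up exists. It does not remove the point, because the article states an explicit cut-off and none of its text points to a later contact.

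**The safety comparison is descriptive in any case.** With so few events expected and a trial sized on procedure time, this is true. It is a reason for a moderate grading. It does not justify recording known types of outcome event as absent.

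**Conclusion.** The point holds for the secondary safety outcomes. The entry rule in Study organization is narrower than the outcomes in Secondary outcomes and Definitions, and a delayed event after first discharge would be analysed as a non-event unless serious-event reports happen to be added to the database.

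The number lost is unknown. The figure of about 0.3–1.2 delayed bleeds per arm rests wholly on the assumed 4–6% risk and 20–50% late share; neither comes from the documents. The conclusion also assumes that the full protocol and the unseen diagram add no later collection point.

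The primary outcome, its analysis and the sample size are unaffected: procedure time is complete when the lesion is resected. Severity is moderate.

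**What to change.** 1. In Study organization, replace the cut-off at first discharge with one fixed observation window counted from ESD, the same in both arms and extending past discharge. About 4 weeks is an example; the documents do not dictate a length, so the investigators should choose and justify one.
2. In Definitions, state that delayed bleeding and delayed perforation are counted within that window.
3. State that readmissions and events reported as serious within the window are entered into the INDICE database as outcome data.
4. Complete the window by chart review or one telephone check per patient. The article describes no outpatient contact after ESD, so the plan should name the source and not presume one.

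The cost is a change of wording in the protocol and the case report form, and a small follow-up effort for 82 patients. Randomization, the primary analysis and the sample size stay as they are. If the full protocol already provides a later contact, only the article's wording needs to be reconciled with it.

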#### Exclusion criteria

Patients who meet at least one of the following exclusion criteria are considered ineligible for this trial: history of gastric surgery, are currently undergoing dialysis, or requiring continuous administration of heparin during the perioperative period. The concomitant use of other antithrombotic agents will be permitted during the study period. The Japanese guidelines for gastroenterological endoscopy for patients undergoing antithrombotic treatment will be adopted for the management of antithrombotic agents to the enrolled patients [15]. Those with contraindications for endoscopy, ileus, gastrointestinal perforation, or severe respiratory/cardiac disease are also excluded as are patients with metal allergies and those judged to be inappropriate for the study by the attending physician in this trial. Those who do not provide informed consent will also be excluded.

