### Statistics

#### Hypotheses and data analysis

The primary efficacy endpoint is the procedure time of the ESD. The null hypothesis is that the procedure time for the H-ESD and C-ESD procedures in patients with EGN is the same.

Analysis of the primary and secondary outcomes will be conducted using the FAS. We plan to analyze complete cases without imputation of missing data because this trial is designed to generate little missing data.

An analysis of covariance for the logarithmically converted ESD procedure time will be conducted with tumor location (upper or middle third of the stomach vs. lower third of the stomach), tumor size (0–9 mm vs. ≥10 mm), and operators’ experience with ESD (0–29 cases vs. ≥30 cases) as covariates. H-ESD will be considered a superior treatment procedure, compared with C-ESD, if the procedure time for H-ESD is significantly shorter than that for C-ESD. A 2-sided *p*-value <0.05 will be considered to indicate statistical significance. In the sub-analysis, if a subgroup factor is one of the covariates, the analysis will be performed without including the sub-group factor as a covariate.

Statistical analyses will be performed by independent statisticians at the Data Center of the Center for Clinical and Translational Research (CCTR) at Kyushu University Hospital. The data will be transferred to SAS statistical software version 9.4 (SAS Institute INC., Cary, NC, USA) for all analyses.

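### The rule for ending participation after randomisation is not separated from ending outcome collection, so a few patients with complications could drop out of the FAS or lose later safety data

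*Protocol article*

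**What the plan says.** All references are to the protocol article.

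- **Study organization** allows an investigator to end participation in the following case: "a participant meets a newly developed or not previously recognized exclusion criterion that precludes further participation, such as the occurrence of a clinical adverse event". Other medical conditions, and situations in which continuing is not in the patient's interest, are further grounds. The section does not say whether outcome data are still collected afterwards. It also has investigators enter endoscopy, pathology and adverse-event data up to first discharge.
- **Exclusion criteria**: "Those with contraindications for endoscopy, ileus, gastrointestinal perforation, or severe respiratory/cardiac disease are also excluded". The need for continuous perioperative heparin and the attending physician's own judgement of unsuitability are on the list as well.
- **Secondary outcomes** include "endoscopic procedural adverse events, including intraoperative perforation, delayed perforation, and delayed bleeding".
- **Randomization**: "Patients and investigators will not be blinded to the allocated treatment group".
- **Definitions** builds the FAS from everyone enrolled, "excluding those who do not receive study treatment, those with serious non-compliance with ethical guidelines, and those with missing primary endpoint data". From this, the per-protocol set further removes patients who fail the inclusion criteria or deviate significantly.
- **Hypotheses and data analysis** uses the FAS for primary and secondary outcomes alike and adds: "We plan to analyze complete cases without imputation of missing data".

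**The concern.** Eligibility is normally judged once, before allocation. Here the exclusion criteria can be applied again afterwards, by someone who knows the arm, with an adverse event as the named example. Because perforation is on both the exclusion list and the outcome list, a complication of the assigned procedure can supply the ground for ending participation. The rule is discretionary, so it could be used differently in the two arms.

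Two things are at stake. One is the safety comparison, where events are few and each one counts. The other, to a lesser degree, is the primary comparison, if the procedures lost before completion would have been long ones. The abstract promises high-quality data on risks as well as benefits.

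**Working it through.** **1. The plan's own figure.** Sample size estimation gives a difference of 0.2 and an SD of 0.3 on the log10 scale (10^-0.2 = 0.631, the stated 37% reduction), with 80% power and two-sided 0.05. The exact two-sample t-test needs 36.3, hence 37 per arm or 74 in total (power 80.8%), as stated. For dropout, 74 × 1.1 = 81.4 gives the stated 82, while 74/0.9 = 82.2 would give 83. This point does not turn on that difference. I use 82/2 = 41 per arm.

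**2. What termination does, by timing.** Study organization is set against Definitions and the analysis section.

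| Participation ends | Procedure time | In the FAS? | Safety data |
|---|---|---|---|
| After allocation, before ESD | none | No: untreated | none |
| During ESD, before resection is complete | may be missing | No, if missing | perforation leaves with the patient |
| After resection | recorded | Yes | events already recorded stay; later pathology, delayed bleeding or delayed perforation are lost only if collection stops |

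In the first two rows the loss follows from the FAS definition once treatment or procedure time is absent. In the third row it depends on what ending participation means. The intervention is a single procedure, so what remains of participation afterwards is essentially data collection to first discharge.

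**3. Safety counts.** The documents give no perforation rate, so these rates are assumptions. Expected events per arm are 41 × rate:
- 2%: 0.8
- 5%: 2.1
- 10%: 4.1

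If one patient with a perforation leaves the FAS (second row of the table), the observed rate changes as follows:
- 1/41 = 2.4% becomes 0/40 = 0%
- 2/41 = 4.9% becomes 1/40 = 2.5%
- 4/41 = 9.8% becomes 3/40 = 7.5%

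**4. Primary outcome, upper bound.** Assumptions: 41 per arm, log10 SD 0.3, no true difference, unadjusted t-test, 40,000 simulated trials, and the k longest H-ESD times removed with none removed from C-ESD.

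| k | Shift (log10) | Apparent reduction | Significant in favour of H-ESD (nominal 2.5%) |
|---|---|---|---|
| 0 | 0.000 | 0% | 2.4% |
| 1 | -0.016 | 4% | 4.8% |
| 2 | -0.030 | 7% | 7.5% |
| 4 | -0.055 | 12% | 14.6% |

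This is a worst case. It requires the lost patients to be exactly the longest, all in one arm, and all without a recorded time.

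**5. Power.** Random loss hardly matters. With difference 0.2 and SD 0.3, power is 84.7% at 41 and 41, and 83.7% at 41 and 39. The issue is selection, not numbers.

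**The case against.** The strongest reply is that nothing in the documents makes termination a reason to leave the analysis. The FAS has three listed exclusions, and neither termination, nor a newly met exclusion criterion, nor an adverse event is among them. Perforation is also expected to be handled inside the trial. Endoscopists and equipment allows a recorded handover when it occurs, Endoscopic procedures provides for a change of technique in C-ESD and requires adverse events to be treated and recorded, and Serious adverse events sets the reporting path. The exclusion list reads most naturally as conditions present before enrolment, and the termination rule is permissive. Finally, a condensed article may leave data handling after discontinuation to the full protocol.

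Most of this stands, and it rules out a stronger reading that a reader might infer: that a patient who perforates and has a recorded procedure time can simply be taken out of the comparison. That patient stays in the FAS, and the complete-case rule drops missing values, not recorded ones. For the same reason one cannot argue that losing a completed 120-minute H-ESD case would shift the arm mean by (2.079 - 1.378)/41 = 0.017, where 1.378 = 1.578 - 0.2. A completed case has a time and is analysed. Nor does the fall from 2/41 to 1/40 apply to a completed procedure. Delayed events occur after the primary endpoint is complete, so those patients already qualify for the FAS.

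The reply does not remove the rest. The article states the conduct rule itself, including reassessment against newly developed criteria and the adverse-event example, so this is more than silence. Combined with the FAS definition as written, it removes patients whose participation ends before treatment or before resection. An analysis plan cannot recover outcomes that were never collected.

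**Conclusion.** The point holds in a limited form. Ending participation does not by itself exclude anyone from the FAS. It leads to exclusion when it happens before ESD or before resection is complete and leaves no procedure time, and the patient's safety outcome then goes too. After ESD it can cost later pathology and delayed-event data, but only if collection stops, which the document leaves open.

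The effect is small: probably no more than one or two patients, which is my assumption. It matters most for reported perforation rates, where one patient may be a large share of an arm's events. For procedure time, the 0.016 to 0.030 shift for one or two removals is a ceiling under deliberately adverse assumptions, and the planned covariate-adjusted analysis was not simulated. The documents do not show that terminations would be frequent, differ by arm or fall on long procedures. This is a wording gap worth closing, not a flaw that undermines the primary comparison.

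**What to change.** Amend Study organization to state that:

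- eligibility for analysis is fixed at randomisation;
- a condition that arises or is recognised later, including an adverse event, does not stop collection of procedure time, pathology and adverse events to first discharge, unless the patient withdraws consent;
- such patients stay in their allocated arm.

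In Definitions and in Hypotheses and data analysis, analyse adverse events in all treated patients whether or not procedure time is missing. Report terminations and late-found ineligibility by arm. Exclude ineligible patients only from the per-protocol set, whose definition now names the inclusion criteria but not the exclusion criteria.

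Exclusion criteria, Endoscopists and equipment, Endoscopic procedures, Definitions and Study organization should be reconciled so that they agree on what happens to a patient's trial data after a perforation or other complication. The change concerns data and analysis only and leaves clinical care as it is.

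The cost is a short amendment. It needs no extra visits or patients, because the data come from the same admission. The downside is that a few patients found ineligible late stay in the main analysis.
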